## Background

This study responds to a number of recent trends: the increasing prevalence of diabetes, the accumulating evidence of the relationship between diabetes and cancer
[1] and the increasing number of options available for treating diabetes. The overall aim is to elucidate the relationship between diabetes and cancer incidence (overall and specific cancers, including second primary neoplasms). Specifically, this is a ten year nationwide population-based investigation of the associations of cancer incidence with diabetes, glucose control and glucose-lowering medications.

To the best of our knowledge, a relationship between glucose control and cancer has not yet been examined. Since glucose control has been found to associate with both micro- and macrovascular complications of diabetes, and cancer is now considered a complication of diabetes, investigation of the effect of glucose control on cancer risk is relevant. Further, data on glucose control is important for the investigation of glucose-lowering medications, since initiation of treatment and switching between treatments may be related to patients’ glucose control.

The use of glucose-lowering medications has been associated with cancer incidence. Sulfonylureas and injected insulin have been found to associate positively with cancer risk
[2-5]; and metformin, which improves insulin sensitivity and lowers insulin levels, to be associated negatively with cancer risk, and to possibly have a protective role
[2-7]. A number of studies reported elevated incidence of malignancy following the use of insulin glargine
[8-10], though their methodologies have been seriously challenged
[11-14]. In particular, the Hemkens et al. study
[9] was widely criticized
[15-17] for not considering such factors as current health status, type of diabetes, intensity of glucose lowering treatment, concomitant medications, BMI, glucose control (HbA1c), hormone replacement therapy, smoking status, and cancer screening. More recently, others have tried to overcome biases by comparing glargine to human insulin, while excluding other insulin analogs
[18], or by including only individuals with type 2 diabetes
[19]. Nevertheless, those studies were criticized for short follow-up periods. Siussa et al.

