### Potential confounders

The following variables will be included together with the time they were recorded:

1. Age, gender, BMI, type of medical insurance (basic, or basic and supplementary).

2. Smoking status (non-smoker, former smoker, current smoker)

3. Concomitant medications (types, exposure rates, and cumulative exposures), including antihypertensive, lipid lowering, beta-blockers, angiotensin converting enzyme (ACE) inhibitors

4. Comorbidities defined according to the Clalit Registry of Chronic Diseases, with focus on those associated with cancer risk (e.g. IBD, COPD, gallstones)

5. Blood pressure (mean annual values)

6. Reproductive factors: hormone replacement therapy, fertility treatments

7. Biochemical characteristics (first and last tests during follow-up, mean annual values, and number of blood tests performed annually): serum lipids (total cholesterol, triglycerides, HDL-cholesterol, VLDL-cholesterol), liver enzymes, creatinine, and urine protein

8. Clinical examinations (average annual number of visits to the treating physician during follow-up)

9. Cancer screening tests: mammography, fecal occult blood, colonoscopy, PAP smear, colposcopy, prostate screening (PSA, ultrasound)

10. Medical procedures associated with cancer risk (e.g. cholecystectomy).

We note that data on some key potential confounders (like smoking and fertility treatments) are available for only a subset of the cohort. We will conduct sensitivity analyses in these subsets to assess whether these factors indeed confound the associations between diabetes, glucose-lowering medications, and cancer.

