### Statistical analyses

For our first specific aim, we will compare, after adjustment, all and site-specific cancer rates between individuals with and without diabetes. For the second aim, we will investigate whether metabolic control, as indicated by HbA1c and blood glucose levels, is related to cancer risk. Third, we will evaluate differences in outcomes that associate with the use of one or a combination of glucose-lowering treatments. In all of these analyses we will stratify persons with diabetes by those who were already diagnosed with diabetes at study entry (prevalent diabetes), and those who were diagnosed during follow-up (incident diabetes).

Preliminary data analysis will employ standard methods, starting with calculation of person years and age-gender standardized cancer incidence rates for all sites and selected sites in non-diabetics, and in prevalent and incident diabetics without prevalent cancer. These methods will also be used to investigate potential confounding variables such as baseline smoking status and body mass index. In our analyses of Specific Aims 2 and 3, we will then proceed to use Cox regression with time-dependent treatment variables. For Specific Aim 2, the model will include current and past levels of Hba1c and blood glucose, investigating the level above selected thresholds cumulated over the past n years, where n may be between 1 and 5. For Specific Aim 3 the model will include current and previous treatments. For example, we will investigate exposure to a specific medication when expressed by the cumulative dose or by the cumulative dose over the past 1–5 years. We will investigate exposure to multiple medications, first by models that postulate independent multiplicative effects on cancer incidence rates (no interaction model); and if there are sufficient data, we will proceed to examine interactions between medications on cancer incidence. Due to data limitations, it is unlikely that anything more than pairwise interactions will be able to be examined satisfactorily. The analyses of glucose-lowering medications will take into account the clinical factors (HbA1c, fasting glucose) that may have triggered the change. We will, for example, use the methods of Walker, White, and Babiker

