The primary analysis will be performed using PROC PHREG of SAS version 9.2, which allows both Cox-proportional hazards models with time-dependent variables and piecewise exponential models. The piecewise exponential model divides time-at-risk into a set of pre-specified intervals with constant baseline hazard in each interval; the use of multiple intervals allows the hazard to vary with time. Clinically important time dependent covariates for the regression models include age, cholesterol (total, LDL, and HDL), concomitant medications (such as statins, beta-blockers, angiotensin converting enzyme inhibitors, and hormone replacement therapy), smoking, body mass index, blood pressure, co-morbidities (such as cardiovascular disease), and reproductive history. For each continuous variable, we will investigate appropriate transformations and interactions that might improve goodness-of-fit. The proportional hazard assumption will be evaluated using log-log survival plots, examination of Schoenfeld residuals, and testing of interactions between variables and time.

While we can not describe, or even anticipate, every contingency for this comprehensive project, we are confident that the very well qualified team has the expertise to evaluate the data.

This study was approved by the ethics committees of Sheba Medical Center, Tel Hashomer and Clalit Health Services, Israel.

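### One time-updated covariate list, including cardiovascular disease, serves all aims, so the Aim 2 hazard ratio (and Aim 1's, if the list applies) can differ from the total association

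*Protocol article*

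**What the plan says.** Under Statistical analyses, "The primary analysis will be performed using PROC PHREG of SAS version 9.2", as a Cox model with time-dependent variables or a piecewise exponential model. The covariates follow directly: "Clinically important time dependent covariates for the regression models include age, cholesterol (total, LDL, and HDL), concomitant medications", then smoking, body mass index, "blood pressure, co-morbidities (such as cardiovascular disease), and reproductive history". The named drugs include statins, beta-blockers and ACE inhibitors. Nothing limits the list to one aim.

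The same section assigns time-dependent Cox regression to Aims 2 and 3 by name. In Aim 2 the exposure is current and past HbA1c and glucose, cumulated over the past 1 to 5 years. For Aim 1 it says only that "we will compare, after adjustment, all and site-specific cancer rates between individuals with and without diabetes".

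Under Potential confounders, "The following variables will be included together with the time they were recorded". The biochemical item takes first and last tests during follow-up and mean annual values, and it includes "liver enzymes, creatinine, and urine protein". That section also notes that "data on some key potential confounders (like smoking and fertility treatments) are available for only a subset of the cohort".

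The Background gives as part of the rationale that "glucose control has been found to associate with both micro- and macrovascular complications of diabetes".

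**The concern.** Cardiovascular disease is the macrovascular complication. The plan's own rationale therefore links to glucose control a variable that its primary model then adjusts for, using values that may be recorded after the exposure.

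This can do two things. If part of any association with cancer runs through such a variable, adjusting for it removes that part. If the variable shares a cause with cancer that is poorly recorded, adjusting for it can create an association between exposure and that cause. Smoking is the obvious candidate, because it is recorded for only a subset.

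At stake is what the Aim 1 and Aim 2 hazard ratios mean. Those aims ask whether diabetes, or glucose control, is associated with cancer. A coefficient conditional on later cardiovascular disease, blood pressure and lipids answers a narrower question, and the plan does not say whether a total or a direct effect is intended. The cohort is large enough for a shift of a few percent to exceed random error.

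**Working it through.** No figure in the plan is disputed here, so there is none to reproduce. The check has three parts.

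**1. Which variables and aims are covered by the text**

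- Cardiovascular disease: in the model list, and linked by the Background to glucose control.
- Blood pressure, lipids and related drugs: in the model list, but not called complications anywhere.
- Creatinine and urine protein: listed as potential confounders only. Their time-updated use in the models is an inference.
- Aim 2: time-dependent Cox is stated. With a window of 1 to 5 years, a currently updated covariate is recorded after much of the exposure.
- Aim 1: applying the list is the natural reading, since no other adjustment set is given, but it is not stated.
- Prevalent diabetes: every follow-up value comes after onset.

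**2. Possible size (all inputs assumed)**

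Expected-value cohort over 10 years, with E the exposure, C(t) time-updated cardiovascular disease and U an unrecorded shared cause:

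- cancer hazard = 0.008 per year × HR_E^E × HR_C^C(t) × HR_U^U
- cardiovascular onset rate = 0.012 per year × RR_EC^E × RR_UC^U
- RR_EC 1.5 to 3; HR_C 1.0 to 1.5; U present in 30%, independent of E; RR_UC 1 to 3; HR_U 1 to 2
- fit: piecewise exponential (Poisson) model for E, without and with C(t)

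| Setting | Without C(t) | With C(t) |
|---|---|---|
| HR_E = 1.2, whole input range | 1.20 to 1.28 | 1.16 to 1.20 |
| HR_E = 1.2, all inputs at their upper ends | 1.28 | 1.16 |
| HR_E = 1.2, HR_C = 1, no shared cause | 1.20 | 1.20 |
| HR_E = 1.0, HR_C = 1, shared cause only | 1.00 | as low as 0.97 |

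The reverse error also exists. If cardiovascular disease precedes exposure and is twice as common in the exposed (20% against 10%), leaving it out gives 1.22 to 1.26 for a true 1.20.

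**3. Random error in Aim 1, all cancers**

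From the protocol: 2,300,000 persons, 110,000 with prevalent and 350,000 with incident diabetes, at least 175,000 cancers, 10 years. Assumed: full follow-up, incident cases contributing 5 years on average, and cancers spread in proportion to person-years.

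- Total: 2,300,000 × 10 = 23,000,000 person-years.
- Prevalent: 1,100,000 / 23,000,000 × 175,000 ≈ 8,370 cancers.
- Incident: 1,750,000 / 23,000,000 × 175,000 ≈ 13,315 cancers.
- Without diabetes: 175,000 − 8,370 − 13,315 = 153,315 cancers.
- 95% half-width on the log scale = 1.96 × √(1/d₁ + 1/d₀).
- Prevalent: 1.96 × √(1/8,370 + 1/153,315) ≈ 0.022, about 2.2%.
- Incident: 1.96 × √(1/13,315 + 1/153,315) ≈ 0.018, about 1.8%.

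The two groups are kept apart because the plan stratifies by them. A 3% shift (1.00 to 0.97) exceeds either half-width; a shift of 1% does not.

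**The case against.** A reader might infer that the plan itself treats blood pressure, lipids, kidney markers and drugs as complications of diabetes and then adjusts for them. It does not. The Background speaks only of an association with micro- and macrovascular complications, and kidney markers are absent from the model list. That part of the objection stands.

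A reader might also infer that the hazard ratios must move downward. The documents do not support this either. A mediator acting against the exposure would move them upward. The collider illustration assumes that the shared cause is wholly unrecorded and unrelated to exposure, whereas smoking is known for a subset, is in the model list, and has sensitivity analyses planned. If smoking is related to diabetes (assumed odds ratio 1.3, true hazard ratio 1.0, smoking hazard ratio 1.5 to 2, cardiovascular onset 1 to 2% per year), the hazard ratio is 1.02 to 1.04 without cardiovascular disease and 1.007 to 1.02 with it. Adjustment then helps, because cardiovascular disease partly stands in for the missing smoking data. This also stands, and it removes any claim about direction.

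Third, the plan reports age- and gender-standardized rates by diabetes status. Those carry no such adjustment, so the total association does appear, but only as preliminary analysis without other confounders.

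Finally, aim-specific covariate sets are often left to a fuller document. The point does not rest on an omission, however: the article names a common time-updated list for its primary analysis. The planned safeguards do not address it as stated. Moving cancer diagnoses back in time targets reverse causation. Lagged predictors can still be post-exposure. Propensity scores are not restricted to pre-exposure values. The prior event rate ratio method is for medications.

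**Conclusion.** The point holds in limited form. It is clearest for Aim 2, where the time-dependent model is explicit, and conditional for Aim 1, where the list is only the natural reading. Followed as written, the model adjusts for values that may be consequences of the exposure, and no total or direct effect is defined. The adjusted hazard ratio can therefore differ from the total association.

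The amount is not fixed by the documents. The illustrations run from no shift to 1.28 against 1.16, and from 1.00 to 0.97 under the null. They rest on assumed rates, on assumed links between exposure, cardiovascular disease and cancer, and on an unrecorded shared cause that is independent of exposure. The half-widths of about 2.2% and 1.8% rest on assumed follow-up and average cancer rates, and apply only to all cancers in Aim 1. It would go too far to say that the results are necessarily distorted, or that Aims 1 and 2 cannot be answered. The same variables can be genuine confounders before exposure, so simply dropping them is no remedy.

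**What to change.** In Statistical analyses, state that Aims 1 and 2 target the total association. For each outcome, report two models side by side:

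- **Pre-exposure model.** Use covariates last recorded before exposure, with attained age updated. For incident diabetes this means before onset, with values at a matched calendar time or age for the diabetes-free. Fixing everyone at study entry would miss confounders that arise before a later onset. For Aim 2 it means before the start of the glucose window.
- **Full time-updated model.** Use the present list, labelled as not a total-effect estimate.

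For prevalent diabetes, where true pre-exposure values are unavailable, report models with and without cardiovascular disease, blood pressure, lipids and related drugs, and kidney markers if they are used. For Aim 2, a marginal structural model is an option for covariates that are both confounders and consequences of earlier glucose control.

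The cost is a change of wording and one extra model per outcome, from data already being extracted. Covariate values will be somewhat older and less complete. Insurance is required only from January 2001, so with a five-year window pre-window values are assured only from 2001 + 5 = 2006 onward.

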## Discussion

Though randomized controlled trials (RCTs) are considered the gold standard for medical research, large long-term RCTs on the relationship between diabetes and cancer incidence are not feasible (due to high costs and resources), may not be the best way to achieve relevant results (due to the time required, low number of events, and sample selection bias), and are subject to ethical problems (by randomly allocating to treatment groups). Specifically, now that the American College of Physicians (ACP) (February 2012)
[23] has strongly recommended monotherapy with metformin as first-line oral therapy for type 2 diabetes, the conduct of RCTs comparing monotherapy glucose-lowering medications, ie. comparing metformin with other oral therapies, would seem unethical.

The advantages of studies based on health insurance administrative databases have become recognized over recent years
[24,25]. Moreover, historical cohort studies afford timely and ethical means of comparing effects of glucose-lowering medications, albeit with methodological challenges. Recently, a nested case control
[26] and cross-sectional study
[7] adjusted for a number of confounding variables before concluding that metformin has a protective effect on cancer outcomes. However, those investigations did not compare the diabetes patients to a non-diabetic population, nor analyze by cancer type. Currie et al., on the other hand, recently reported decreased mortality among cancer patients using metformin, even compared to those without diabetes, and increased survival among metformin users for most cancer sites, but not for breast cancer
[27]. The fact that increased breast cancer was also reported among insulin users, compared to other cancer types
[19,28], suggests that such differences may be due to confounding factors rather than to the effects of medications. Most studies did not account for surveillance bias, ie. the possibility that the detection of cancer may differ between those with and without diabetes, resulting in a spurious difference in cancer incidence between the two groups. The observation that women with diabetes were found to screen less for cancer than women without
[29,30] highlights the importance of mitigating surveillance bias.

The current study will undertake various means to deal with the challenges posed by recent investigations, including comparison to a large population of individuals without diabetes in a nationwide population, and accessing a large number of potentially confounding factors and data on cancer screening.

Statistical power is expected for a number of monotherapies and combination treatments among individuals newly diagnosed with diabetes, thereby controlling for the duration of diabetes and for all glucose-lowering medications used during the course of their treatment. Temporal relationships between diabetes and cancer will be considered. A number of aspects of the study design are expected to elucidate the complex relationship between diabetes and cancer, and possible effects of glucose-lowering medications: analysis of data preceding diabetes incidence, the inclusion of “no glucose-lowering medications” as an exposure, and the inclusion of all individuals with and without diabetes who were insured by one very large health maintenance organization during a ten year period.

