## Methods/design

This is a large scale historical cohort study of all adult individuals insured by Clalit Health Services, the largest health maintenance organization in Israel, insuring and providing healthcare to 55% of the Israeli population (about 3.9 million people). Study entry is defined as January 1, 2002. Inclusion criteria will be: age 21 years or older at study entry and continuous insurance in Clalit Health Services from at least one year prior to study entry, January 1 2001, until the end of the study period, December 31, 2011, or until death, for those who do not survive until the end of follow-up. Of the population of over 2,300,000, over 110,000 had diabetes at study entry; and an additional 350,000 were diagnosed with diabetes during the study period (January 2002 to December 2011).

This study has three Specific Aims: First, we will compare rates of cancer incidence (overall and specific cancers, including second primary neoplasms) in individuals with and without diabetes (separately for prevalent and incident cases of diabetes). Second, we will investigate, in individuals with diabetes, the associations between measures of glucose control, as assessed by HbA1c and fasting plasma glucose, and cancer incidence (overall and specific cancers, including second primary neoplasms). Third, we will compare the incidence of cancer (overall and specific cancers, including second primary neoplasms), among individuals with diabetes who used specific glucose-lowering medications, as well as among patients with no drug exposure (periods of time during which individuals classified with diabetes did not yet purchase glucose-lowering medications, including periods on diet and exercise regimen only).

Four study groups will be established according to the status of diabetes and cancer at study entry, Jan 1, 2002 (Figure
1): cancer free, diabetes free (CF-DF); cancer free, diabetes prevalent (CF-DP); cancer prevalent, diabetes free (CP-DF); and cancer prevalent, diabetes prevalent (CP-DP). Individuals free of diabetes at study entry will be followed for diabetes incidence, and all four groups will be followed for cancer incidence (second primaries for those with prevalent cancer). Nine groups, according to diabetes and cancer prevalence at study entry, and diabetes and cancer and incidence during the study period, will be analyzed (Figure
2).

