### Exposure to glucose-lowering medications

In addition to the exposure to diabetes per se, individuals with diabetes will be studied for their exposure to glucose-lowering medications. A drug exposure will be defined as a minimum of 3 purchases of glucose-lowering medications during one year. Each drug exposure will define one type of treatment or a combination of treatments. An individual may be analyzed according to more than one exposure during follow-up time. Drug exposures to be investigated are: each insulin type, meglitinide derivatives, sulfonylureas, biguanides, alpha glucosidase inhibitors, thiazolidinediones, and incretins. An additional group (“no glucose-lowering medication”) will comprise periods of time during which individuals classified with diabetes did not yet purchase glucose-lowering medications.

For each glucose-lowering medication, cumulative exposure will be assessed as the total number of monthly dosages purchased. Daily dosages and daily dosages per body weight will be estimated from records of purchases. Time dependent regression models for the outcomes investigated will account for glucose-lowering medications as they are added and changed over the follow up period, adjusting for constant and time-dependent covariates.

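### Studying newly diagnosed people does not by itself control diabetes duration, and the article states no other adjustment for it

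*Protocol article*

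**What the plan says.** - Discussion: power is expected for monotherapies and combinations "among individuals newly diagnosed with diabetes, thereby controlling for the duration of diabetes". The same paragraph presents the no-medication category as a design strength.
- Methods/design: about 350,000 people "were diagnosed with diabetes during the study period (January 2002 to December 2011"). The one origin given is "Study entry is defined as January 1, 2002".
- Exposure to glucose-lowering medications: the no-drug category is "periods of time during which individuals classified with diabetes did not yet purchase glucose-lowering medications". For drug use, "A drug exposure will be defined as a minimum of 3 purchases of glucose-lowering medications during one year". Cumulative exposure is the number of monthly dosages purchased.
- Statistical analyses: all analyses are stratified by prevalent versus incident diabetes. On adjustment, "Clinically important time dependent covariates for the regression models include age, cholesterol (total, LDL, and HDL), concomitant medications" and further items (smoking, BMI, blood pressure, comorbidities, reproductive history). The piecewise exponential model splits time at risk into intervals, without saying where time at risk begins.
- Potential confounders: ten items. Neither diabetes duration nor diabetes type is among them.
- Background: an earlier study was criticized "for not considering such factors as current health status, type of diabetes, intensity of glucose lowering treatment" and other factors.

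**The concern.** Restriction to incident cases excludes long-standing recorded diabetes at baseline. It does not hold duration constant afterwards. Someone diagnosed in early 2002 contributes time at almost every duration up to ten years, and treatment changes along the way. The no-drug category ends at the first purchase, so it is early-duration time by construction. Cumulative dose can only grow as time since diagnosis grows. Duration is therefore tied to both forms of the drug exposure.

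If cancer rates also vary with time since diagnosis, for any reason, part of that variation will be read as a drug effect unless people are compared at the same duration. The Discussion sentence tells readers that this has been dealt with, but nothing stated in the article does it. The no-drug comparison, which the article counts among its strengths, is the most exposed.

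**Working it through.** **The plan's own figure, as a yardstick.** Power calculation gives over 80% power for a hazard ratio of 1.4 with two subsets of 6000, two-tailed 0.05. Schoenfeld's formula with equal groups gives 4 × (1.960 + 0.842)² / (ln 1.4)² = 278 events, or 278/12,000 = 2.3% of the two subsets. The event rate in those subsets is not given, so the statement can be confirmed only as a lower bound; this point does not depend on it. Inverting the formula, the smallest hazard ratio detectable with 80% power is exp[2 × 2.802/√d]: 1.28 at d = 500 events and 1.19 at d = 1000, the subset sizes the section names. The reciprocals are 0.78 and 0.84.

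**Model for the bias.** Only the ten-year window comes from the document. Assumed: the true drug hazard ratio is 1, diagnosis dates are uniform over the window, time to first drug is exponential with mean m years, and there is no loss to death. At duration t the person-time densities are

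- no drug: n(t) = exp(−t/m) × (1 − t/10)
- drug: d(t) = [1 − exp(−t/m)] × (1 − t/10)

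**Duration by exposure.** For m = 1, 2, 3 years, mean duration is 0.9, 1.5, 1.9 years in no-drug time and 3.9, 4.2, 4.4 years in drug time. The imbalance does not depend on how cancer rates behave.

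**Early excess.** If the rate is multiplied by f up to duration w, the crude ratio is [1 + (f − 1)s_d] / [1 + (f − 1)s_n], where s_d and s_n are the shares of drug and no-drug time lying below w. For m = 1 and w = 0.5:

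- no-drug time below w is 0.384 out of 0.900, so s_n = 0.427
- all time below w is 0.4875, so drug time below w is 0.4875 − 0.384 = 0.103 out of 4.100, and s_d = 0.025
- with f = 2 the ratio is 1.025/1.427 = 0.72

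**Rising rate.** The rate is multiplied by 1.02 or 1.05 per year of duration, with median time to first drug of 1, 2 or 4 years. As a rough check, at a median of 1 year the mean durations are 1.20 and 4.03 years, and 1.05^2.83 = 1.15.

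| Assumed pattern, no true drug effect | Time to first drug | Crude drug/no-drug ratio |
|---|---|---|
| Flat rate | any | 1.00 |
| 1.5-fold for 3 months | mean 1, 2, 3 y | 0.90, 0.93, 0.95 |
| Doubled for 6 months | mean 1, 2, 3 y | 0.72, 0.80, 0.84 |
| Rising 2% per year | median 1, 2, 4 y | 1.06, 1.05, 1.04 |
| Rising 5% per year | median 1, 2, 4 y | 1.15, 1.13, 1.11 |

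Comparing people at the same time since diagnosis returns 1.00 in every row, by construction.

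**The case against.** **The model may already control duration.** The covariate list is introduced as open, and the time axis is unstated. Age enters as a time-dependent covariate, which suggests that it is not the axis. If time at risk in the incident stratum starts at diagnosis, the Cox risk sets or piecewise intervals control recorded duration without any covariate. A condensed article may leave this to a fuller plan. This stands as far as it goes. A reader might infer that duration is in no model and that the contrast is in fact confounded; the document shows neither. It does state one origin, which is not diagnosis, and it credits control to restriction rather than to the time axis.

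**The lag analyses.** Statistical analyses will examine results with cancer diagnoses moved back 6 months, 1 year or 2 years. A 6-month shift would place every cancer from a 6-month peak before the diabetes diagnosis and return the ratio to about 1.00. This is correct for a short peak. But it is a check aimed at reverse causation, not the main analysis. It would only partly remove a longer excess and would leave a steady trend in place. The planned look for early peaks follows treatment changes, not diabetes diagnosis.

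**Direction.** A reader might infer that every drug will look protective. That needs an early peak in cancer detection, which the document neither states nor quantifies; a rising rate reverses the sign. Nor would first-line drugs be affected most under such a peak. With a doubled rate for 6 months and an assumed mean of 3 years to second-line treatment, the ratios against no drug are 0.74, 0.81, 0.85 for first-line and 0.70, 0.79, 0.83 for second-line.

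**Other adjustments.** HbA1c, physician visits, number of blood tests, screening, propensity scores and the prior event rate ratio method may absorb some of the effect, and the ratios above are crude. None of these is stated to include duration.

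**Diabetes type.** The article gives no count of type 1 among newly diagnosed adults, so no size can be put on mixing the types. It supports a sensitivity analysis and nothing stronger.

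**Conclusion.** The point holds in limited form. The Discussion attributes to restriction a control that restriction does not give, and following the one stated origin and the two covariate lists leaves duration tied to drug exposure. The drug versus no-drug and cumulative-dose contrasts are open to confounding by duration; they are not shown to be confounded.

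The size rests wholly on assumed rate patterns and times to first drug: from no bias, through roughly 5-10% for a mild short peak and 16-28% for a doubled 6-month rate, to 4-15% the other way for a rising rate. The larger values reach the effects that subsets of 500-1000 events could detect.

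Diabetes classification adds a caveat. The definition before 2002 was narrower, so some incident cases may have older diabetes, and any adjustment controls recorded duration only.

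**What to change.** 1. In the incident-diabetes models for Aims 2 and 3, use time since diabetes diagnosis as the time axis, with attained age as a covariate. Alternatively, enter time since diagnosis as a time-dependent covariate with fine early bands, for example 0-3, 3-6 and 6-12 months, 1-2, 2-5 and over 5 years.
2. Reword the Discussion sentence to say that duration is controlled by this adjustment, not by restriction alone.
3. As a secondary sensitivity analysis, repeat the insulin analyses without probable type 1 cases flagged from recorded data, such as insulin-only purchases from diagnosis together with young age at diagnosis.

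No new data are needed, because diagnosis dates, ages and purchases are already recorded. The cost is slightly wider intervals and, in the sensitivity analysis only, setting aside the flagged people.
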